## Methods and analysis

### Study design and conduct

This is a pragmatic, multicentre, randomised controlled parallel group trial in adult patients presenting to the ED with suspected cardiac chest pain and who trigger the chest pain investigation pathway. Five hundred and ninety-four participants will be randomised in a 1:1 ratio to be managed according to the LoDED strategy (allowing discharge after a single hs-troponin test at presentation to ED if a participant has no new ischaemic ECG changes and the hs-troponin is below the LoD) or the usual care rule-out strategy in current clinical use at each study site. Usual care will usually include two hs-troponin blood tests taken between 1 and 6 hours after presentation and may vary between sites.

This is an open study. Participants’ study allocations will only be blinded to those performing central review of data for the assessment of outcomes and the statistician analysing the results. All patients will be consented and randomised before their initial hs-troponin results are known. Patients will be ineligible to participate in the trial once the initial hs-troponin result is known to the treating clinician in order to prevent selection bias. The decision to discharge a patient will be made after clinical assessment by the treating clinician. In the event of ongoing clinical concern, the clinician may proceed with further testing and/or admission at their discretion, and contrary to the allocated strategy. Information on protocol adherence will be collected to facilitate a per-protocol analysis as well as the primary intention-to-treat analysis.

The key objective of this study is to conduct a randomised controlled trial (RCT) of the LoDED strategy versus usual care to compare the proportion of patients successfully discharged within 4 hours of arrival, with no MACE during the following 30 days. We will also measure admission rates, hospital bed usage, length of stay, resource use and patient satisfaction, facilitating a health economic evaluation, and determine whether the LoDED strategy is acceptable to patients through qualitative interviews.

Day-to-day trial management is administered through the UKCRC-registered Peninsula Clinical Trials Unit (CTU) at Plymouth University and sponsored by North Bristol NHS Trust.

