#### Baseline blood sampling

All participants will have a blood sample taken for hs-troponin measurement on, or shortly after, ED arrival as part of the standard clinical assessment of patients with chest pain. No additional blood sampling is required for study purposes. All study centres have access to hs-troponin assays which already form part of standard care.

Given the pragmatic nature of the trial, ‘presentation’ blood sampling will be defined as the first blood sample taken after arrival in the ED. Blood sample results will not be delayed for trial purposes.

Standard laboratory reporting of hs-troponin results and other routine baseline blood tests will be used for both clinical assessment and for data collection purposes. At all sites this is through an electronic clinical record. Data from the laboratory system will be anonymously recorded within the case report form (CRF).

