#### LoDED strategy (intervention)

Participants randomised to the LoDED strategy will be eligible for discharge after a normal ECG and single hs-troponin test at presentation to the ED if the hs-troponin is below the LoD for the assay in use at the study centre.

Any participant not fulfilling this discharge criterion will revert to the existing rule-out strategy in use at that study site and have a second hs-troponin test after 1–6 hours as per usual care.

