### Postintervention procedures

#### Clinical management

Once hs-troponin results are available (for either control or intervention pathways) the discharge decision will be entirely at the discretion of the treating clinician. Onward referral for outpatient investigation, such as chest pain clinics, will follow local guidance and will not be altered for trial purposes.

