### Outcomes

#### Primary outcome

The primary outcome is successful early discharge, defined as discharge from hospital within 4 hours of ED arrival, without MACE occurring within 30 days.

The safety endpoint of MACE occurring within 30 days, included within the primary outcome, will be defined as cardiac death, AMI or emergency revascularisation occurring within 30 days of ED attendance (including the index presentation). AMI will be defined according to the universal definition, which states that a rise and/or fall of troponin above the 99th percentile value confirms the diagnosis.^25^ A significant rise and/or fall will be defined as an absolute change in troponin over time of at least half the 99th percentile value of the assay in clinical use.^26^

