### Sample size

Current observational research gives estimates of the proportion of patients with an hs-troponin <LoD in the intervention group of the RCT (LoDED strategy) of between 10% and 60%.^11–17^ UK observational data suggest that these patients will be discharged within a median time of 3.5 hours (taking into account laboratory processing and 60 min of decision-making time).^10^ Data provided to us from a recent pragmatic RCT evaluating a 0/2-hour hs-troponin rule-out strategy have demonstrated that only 10% of patients will be discharged within 4 hours using this approach.^9^ Clinical protocols using rule-out strategies at later time points (eg, 3 hours) will be expected to have even fewer patients discharged within the 4-hour time frame; similarly the 0/1-hour strategy may realise a marginal increase in discharges before 4 hours. These differences have been taken into account within the power calculation. For the overall population we anticipate 8% will be discharged within 4 hours using usual care and at least 17% using the LoDED strategy. Therefore, this study will be powered to detect a 9% difference between the early discharge rates with 90% power and 5% statistical significance. This will require 282 patients in each group and 564 patients in total with primary outcome data. Assuming a 95% follow-up rate, 594 patients need to be recruited. Recruitment will take place over a 9-month period.

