### Data analysis

All analyses will be conducted blind to group allocation. A Consolidated Standards of Reporting Trials diagram will be used to report the number of patients screened, recruited and randomised.^27^ It will also detail the number allocated to each group and the frequency of the primary outcome.

The primary outcome of discharge within 4 hours will be analysed by logistic regression using all those randomised in an intention-to-diagnose analysis. The analysis will be stratified by centre to allow for differences between the proportions discharged within 4 hours in the control group at each of the study sites. Heterogeneity of the odds of early discharge at each centre will be investigated and only pooled if appropriate. The OR of early discharge controlling for age, sex and centre will be presented with a 95% CI for each centre individually and combined across centres. In the event of significant heterogeneity in the control group but homogeneity within the intervention group the results will be presented as the rate of early discharge in the intervention group together with 95% CIs. Adherence to the allocated rule-out strategy will be presented as percentage with 95% CIs.

The analysis of the quantitative secondary outcomes will also control for age, sex and centre, with a multiple regression analysis and difference in means reported for the comparison of length of hospital stay between groups and for the total score from the patient satisfaction survey obtained from summing the individual items. The responses for the individual items of the patient satisfaction survey will also be reported by group, but an adjusted analysis will not be carried out.

The incidence of MACE occurring within 30 days of ED attendance in those discharged according to the LoDED strategy versus usual care will also be reported with 95% CIs. As the event rate is expected to be low, it is unlikely to be possible to carry out an adjusted analysis. There are no preplanned interim analyses. A secondary per-protocol analysis will also be performed for the primary outcome.

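### The per-protocol analysis is tied to a post-randomisation decision that nearly settles the 4-hour discharge outcome, so it is selection-prone; comparing arms as randomised among those below the LoD would be safer.

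*Protocol article*

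**What the plan says.** Under Data analysis, the article makes the analysis of all randomised participants primary and adds: "A secondary per-protocol analysis will also be performed for the primary outcome". It gives no exclusion rule there.

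Study design and conduct says that, where clinical concern persists, "the clinician may proceed with further testing and/or admission at their discretion, and contrary to the allocated strategy". The next sentence reads: "Information on protocol adherence will be collected to facilitate a per-protocol analysis as well as the primary intention-to-treat analysis". This is the only deviation that the article connects to the per-protocol set.

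The primary outcome is "successful early discharge, defined as discharge from hospital within 4 hours of ED arrival, without MACE occurring within 30 days". LoDED participants who meet the rule "will be eligible for discharge after a normal ECG and single hs-troponin test at presentation to the ED" (LoDED strategy section), and under Clinical management "the discharge decision will be entirely at the discretion of the treating clinician".

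On the first troponin, Baseline blood sampling says: "All participants will have a blood sample taken for hs-troponin measurement on, or shortly after, ED arrival". Study design and conduct has everyone randomised before that result is known. Participants below the LoD are followed up in both arms (Follow-up processes) and form a costing and QALY subgroup in both arms (Health economic analysis). Data analysis plans no comparison of the primary outcome in that group.

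**The concern.** A LoDED participant below the LoD who is kept for a second test or admitted will usually miss the 4-hour limit. If that participant counts as non-adherent and is excluded, the exclusion is made on something very close to the outcome. It is also selective on prognosis, because the override is prompted by clinical concern. The LoDED arm then loses mostly failures, and the arms are no longer comparable.

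At stake is how the secondary result is read. A per-protocol estimate above the intention-to-treat estimate invites the reading that this is what the strategy achieves when properly followed, when part of the gap would be selection. Meanwhile, the participants in whom the two strategies actually differ can be identified in both arms from a sample that everyone gives.

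**Working it through.** **Inputs from the article.** Early discharge 8% under usual care and 17% under LoDED; 282 per group with outcome data, 90% power, 5% significance, 95% follow-up (Sample size). Share eligible for early discharge q = 30% for hs-troponin T (Introduction); the range quoted for troponin below the LoD is 10-60% (Sample size). Early discharge on a 0/2-hour serial strategy: 10% (Sample size).

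**Assumptions, not in the article.** Share of eligible LoDED participants overridden and excluded: f = 10-30%. Success rate among those excluded: r = 0 (all fail) to 10% (the 0/2-hour figure).

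**Step 1: reproduce the plan.** Two proportions, pooled variance under the null, two-sided 5%, 90% power, 8% against 17%: 281.7, so 282 per group and 564 in total. 564/0.95 = 593.7, so 594. Both match. The planned OR is (0.17/0.83)/(0.08/0.92) = 2.36.

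**Step 2: effect of the exclusion.** The per-protocol LoDED rate is (0.17 − q·f·r)/(1 − q·f), with the control rate held at 8%.

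| f | r | LoDED rate | Difference | OR |
|---|---|---|---|---|
| 10% | 0 | 0.170/0.97 = 17.5% | 9.5 points | 2.44 |
| 30% | 0 | 0.170/0.91 = 18.7% | 10.7 points | 2.64 |
| 10% | 10% | 0.167/0.97 = 17.2% | 9.2 points | 2.39 |
| 30% | 10% | 0.161/0.91 = 17.7% | 9.7 points | 2.47 |

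The rate rises only if r is below 17%, the LoDED arm's own rate. At r = 17% the difference stays at 9.0 points.

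**Step 3: no true effect (8% in both arms, q = 30%).** By simulation, if all those excluded are failures, the one-sided 2.5% error in favour of LoDED rises to 4.1% at f = 20% and 6.7% at f = 40%. If those excluded succeed 8% of the time, it stays at 2.5%.

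**Step 4: other exclusions.**
- Also removing controls discharged early after one test, equal to 2% of that arm: control rate (0.08 − 0.02)/0.98 = 6.1%. With f = 30% and r = 0, the difference is 12.6 points (OR 3.5).
- Removing 12% of controls, all failures: control rate 0.08/0.88 = 9.1%. With f = 40% and r = 0, the LoDED rate is 0.17/0.88 = 19.3%, the difference 10.2 points and the OR 2.39.
- Removing LoDED early discharges equal to 1% of the arm, with f = 10% and r = 0: 0.16/0.96 = 16.7%, a difference of 8.7 points and OR 2.30, below intention-to-treat.

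**Step 5: the comparison by allocation below the LoD.** At q = 30% there are 282 × 0.30 ≈ 85 per arm. If the whole 9-point effect arises there, the difference within the stratum is 9/0.30 = 30 points. Power is 98% if all control early discharges are below the LoD (26.7% against 56.7%) and 99.8% if the control rate is 8% in both strata (8% against 38%). At q = 60% it is 93-97%.

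**Step 6: optional adjustment of the primary analysis.** The variance of the standardised risk difference, with a below-LoD indicator and its interaction with arm, is [mean within-stratum variance in each arm, summed, + Var(stratum effect)/2]/n, against (0.1411 + 0.0736)/n unadjusted. Three assumed sets of early-discharge rates were used at q = 30%:

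| LoDED, below LoD | Control, below LoD | Both arms, not below LoD | Variance ratio | Power |
|---|---|---|---|---|
| 40% | 10% | 7.1% | 0.94 | 92% |
| 45% | 15% | 5% | 0.88 | 94% |
| 50% | 20% | 2.9% | 0.80 | 95% |

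**The case against.** The strongest reply is that the article never states who is excluded. Permitting an override and recording adherence does not define a per-protocol set; that definition commonly sits in an analysis plan, which is not shown here. This stands: the exclusion rule is inferred, and its absence from a journal article is not itself a fault. What remains is that the one deviation the article names, and ties to this analysis, is unsuitable as an exclusion criterion for this outcome.

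Second, a reader might infer that the per-protocol estimate must exceed intention-to-treat. The documents do not support that. The Sample size section expects 10% to leave within 4 hours on a 0/2-hour strategy, so being kept for more testing is not the same as failing. The wording on deviating from allocation also covers both arms, and step 4 shows that exclusions of control failures or of LoDED early discharges can cancel or reverse the shift.

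Third, a reader might take 12.6 points (OR 3.5) as the likely size. That figure needs a control-arm exclusion that the article does not describe.

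Fourth, the analysis is secondary, intention-to-treat is primary, and adherence will be reported with confidence intervals. All of this is true and limits the consequence. It does not make the per-protocol estimate informative.

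**Conclusion.** The concern holds in a limited form. A per-protocol set based on the override decision would be selected on something close to the outcome. Under the planning rates it would be expected, not certain, to overstate the LoDED effect: about 9.2-10.7 points (OR 2.39-2.64) against 9.0 points (OR 2.36). This rests on 30% eligible, on an assumed 10-30% overridden with 0-10% success among them, and on no other exclusions. The shift is modest, and the primary result is untouched.

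The point is still worth acting on, because a comparison that respects randomisation is available from data already planned. The presentation sample is taken in everyone on or shortly after arrival, its result is unknown at randomisation, and the stratum is followed in both arms. Participants who do not meet the LoDED rule revert to usual care, so this stratum is where the strategies differ.

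**What to change.** 1. Replace the per-protocol analysis, or accompany it, with the primary outcome compared by allocated arm among participants in both arms whose presentation hs-troponin is below the LoD. Describe it as the effect of allocation in those eligible for early discharge.
2. If a per-protocol set is kept, define it for both arms without using the discharge or retention decision, and label the result as selection-prone.
3. Optionally, adjust the primary analysis for presentation hs-troponin below the LoD (yes/no), standardised over all randomised. This is an efficiency gain, not the correction of an error: power rises from 90% to about 92-95% under the assumed stratum rates.

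The cost is analysis-plan wording and a little extra analysis; first troponin results are already recorded on the CRF. The trade-off is that the supportive estimate answers a slightly different question from the effect of full adherence.

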### Health economic analysis

The primary economic analysis will include all randomised participants (intention-to-diagnose analysis) and compare secondary care costs. Secondary care resource use will be valued using national sources of unit costs. A subgroup analysis will provide extra detail on the primary and community care costs (in addition to the secondary care costs) and consequences (quality-adjusted life-years (QALY)) for any participant with an hs-troponin below the LoD. This applies to both trial groups. Data collection for the additional primary and community care costs will be based on participant self-report following administration of a structured resource use questionnaire at 30 days and standard methods of unit costing. QALYs will be derived from the EQ-5D (5-level version) using the set of preference weights recommended by NICE at the time of analysis.^24^

### Integrated qualitative study

The qualitative component of this trial aims to explore the patients’ experiences of the ED, the concerns or anxieties they might have and how best to word patient discharge information. To explore the acceptability of the LoDED strategy to participants and inform patient discharge information resources, a qualitative research assistant will undertake semistructured interviews with a sample of intervention participants. At 30-day follow-up contact, all participants with hs-troponin levels below the LoD will be invited to participate in an interview. From those participants who consent to interview, a purposive sample will be selected across all sites to maximise variation in terms of age, sociodemographic status and gender. Up to 25 participant interviews (lasting approximately 30 min) will be conducted by phone using a topic guide to explore experiences of the participant’s stay in ED, any concerns or anxieties they might have about being discharged early and how best to word and present the written patient discharge information. Consent to take part in the qualitative study will be collected before the interview is carried out. Topic guides will be developed from the literature, input from the patient advisory group and team discussions. Two general practitioners (GP) and practice nurse focus groups will be held towards the end of the recruitment period to explore their views about the information that they would like to be provided to patients who are discharged early. Findings from the participant interviews will contribute to these focus group discussions.

Interviews and focus groups will be recorded, transcribed, anonymised and analysed using thematic methods facilitated by NVivo software (QSR International). Analysis will be ongoing and iterative. Transcripts will be coded and global themes developed from the codes. Two researchers will code a sample of transcripts independently, compare coding, discuss and resolve any discrepancies within the research team to achieve a coding consensus and ensure robust analysis.

### Safety and data monitoring

Observational data have shown the LoDED strategy has a very high diagnostic accuracy.^11–17^ However, no rule-out strategy is 100% accurate, therefore, although there is no formal data monitoring committee, adverse event data will be monitored by the Trial Steering Committee (TSC), to ensure safety. The TSC includes an independent statistician, cardiologist, emergency physician (chair) and a patient and public representative and will meet on four occasions. All suspected SAEs will be reported, within 24 hours of discovery, to the CTU who will notify the Chief Investigator (CI), the TSC and the trial sponsor. All SAEs will be followed up until resolution. If the SAE is considered a MACE, this will be indicated on the SAE form, and will be adjudicated at the end of the study. Following the initial report to the CI of any study-related SAEs, the CI will notify the chair of the TSC within 48 hours of the event. The chair will arrange an ad hoc meeting of the TSC to discuss the SAE, and agree to any actions as needed. The TSC and trial sponsor have the authority to stop the trial if any indication of harm is found.

The CTU data management team is responsible for data management, including data entry. Original CRF pages will be posted to the CTU at agreed time points for double-data entry onto an SQL Server database using a bespoke, password-protected website, designed and maintained by the CTU data programming team.

### Ethics and dissemination

The trial complies with the Declaration of Helsinki and GCP guidelines. All eligible, willing participants will undergo written informed consent by GCP trained staff before taking part in the study.

The results of the study will be applicable and of interest to emergency physicians, acute physicians, cardiologists, GPs and patients. The CI and trial management group (TMG) will establish a writing committee which will be responsible for preparing scientific reports of the study findings. The aim will be to publish a primary manuscript in a high-impact general medical journal, published as open access, with secondary analyses described in specialty journals. Primary findings will also be presented at key meetings, for example, the annual conference of the Royal College of Emergency Medicine, the European Society of Cardiology Annual Congress and the International Conference on Emergency Medicine.

### Patient and public involvement

Patient and public involvement was ensured at all stages of trial design. A prospective quantitative survey of 278 patients with chest pain, performed by our group, has previously demonstrated satisfaction with very early discharge.^28^ The intervention and primary outcome measure of safe early discharge were supported by our patient advisory group. The patient advisory group oversaw development, and approved all patient-facing materials, including PIS, consent forms and discharge information leaflets. There will be continued patient representation on the TMG, TSC and authorship. Lay summaries of trial results will be made freely available to participants and the wider public.

## Discussion

This trial of the LoDED strategy versus usual care is a pragmatic multicentre RCT aiming to establish the clinical and cost-effectiveness of a novel rule-out strategy for patients with chest pain attending the ED using just a single blood test, combined with ECG findings. Should the LoDED strategy prove effective, in a way that is acceptable to patients, it is likely to become widespread practice in those EDs with access to hs-troponin assays. This would have potential benefits to patients around the world, by providing early reassurance and a potential reduction in ED crowding by facilitating earlier discharge.

This is a pragmatic study, being carried out in an environment where patients with chest pain are normally treated, with clinical assessment being undertaken by treating emergency clinicians. In addition, we have selected multiple sites with variable usual care pathways that use a range of commercially available hs-troponin assays. These elements of the study design will enhance the generalisability of the trial findings.

The trial has also been designed to meet its objectives and recruitment targets in the challenging ED environment using a carefully considered effect size and accrual rate, based on data from previous research. We believe the trial will therefore be able to deliver these objectives within the allocated time and resources. Previous and ongoing interventional trials in this area have chosen a step-wedged cluster randomised design which require a larger sample size than individual randomisation, and have had primary outcomes evaluating safety.^18 29^ Given the strength of observational data confirming the high diagnostic accuracy of the LoDED strategy, we have been able to focus on clinical effectiveness as a primary outcome and we have elected to use a parallel group design with 1:1 randomisation. This has allowed us to maximise the efficiency of the trial.

Other rule-out strategies using a single blood test to facilitate early discharge have been considered.^10 18 21 29 30^ However, the LoDED strategy may have advantages over these. First, the hs-troponin test can be applied, on arrival in the ED, independently of chest pain onset time across the study population. This sets it apart from alternative methods currently under evaluation such as HighSTEACS,^29^ which uses a higher Abbott hs-troponin I cut-off value. The HighSTEACS strategy cannot be applied in patients presenting less than 2 hours from symptom onset, which is likely to make it less applicable and effective than the LoDED strategy. Second, other alternative strategies, including those recommended by NICE, require the addition of a risk score such as TIMI.^22^ This may act to reduce the proportion of patients suitable for early discharge when compared with the LoDED strategy.

